
### Data Transfer, Safety, and Privacy

Access to the app is controlled through a 2-factor authentication process. An enterprise environment is created on the health care smartphone using the Microsoft Intune software (Microsoft Corp.), for both Android and iOS operating systems. This environment ensures that the app is run in a secure context where only an authorized app can be installed. This environment also enables the installation of a certificate that serves as a second authentication factor, while the first factor is the user’s login and password. Access rights are managed by the Active Directory group, which enables access to ED caregivers only. All data collected by the app are transmitted securely through a hypertext secure transfer protocol and stored exclusively on the hospital’s secured internal server.

### Data Collection

Electronic data will be extracted from the institutional data lake. The data lake stores all data and events from the EMR information system in a database and can be retrieved using Simple Protocol and RDF Query Language (SPARQL) queries. In the preintervention period, the time stamp of the laboratory results on the EMR will be identified as the time of issuance of the said results. Access to these results by the physicians and nurses will be defined by the time stamp of the first access to the laboratory results’ viewer on the EMR. Access to results on the app will be computed either by the time stamp of the push notification access or to the dedicated page on the app. No other patient-level data such as identifiers or clinical characteristics will be collected. Collected data will be transmitted to the REDCap database web app (REDCap, Vanderbilt University) hosted by the hospital for analysis.

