### Participants

Eligible participants will be postgraduate residents pursuing a less than 6-year residency in pediatrics, pediatric emergency medicine fellows, and registered nurses from the pediatric ED (aged >18 years). Written informed consent will be obtained from each participant in the experimental group after full information disclosure prior to study participation. On the first day, after completing the informed consent form, participants will be asked to download the app to their personal smartphone through the secure institutional Microsoft Intune portal (Microsoft Corporation). They will then be required to attend a unique standardized 5-minute introduction course to the app and its functionality by the study investigators, but they will not receive specific instructions on how often to use the app. The participants will remain the same throughout the intervention period. No one will be asked to advise on the interpretation of the results.

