**Assessments**					
	Case report form (demographics)		✓		
	EMR^b^-based data	✓	✓	✓	
	App-based data		✓	✓	
	UTAUT^c^		✓		✓
	SUS^d^				✓

^a^✓: Performed.

^b^EMR: electronic medical record.

^c^UTAUT: Unified Theory of Acceptance and Use of Technology.

^d^SUS: System Usability Scale.

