### Statistical Analysis

The association of app use with the time between delivery of the laboratory results and their access by caregivers will be assessed using generalized estimating equations with an exchangeable correlation structure to account for the nested structure of the outcome (ie, time) within the physicians. To account for potential differences in case-mix and physician characteristics, we will use multivariable generalized estimating equations. The covariates will be as follows: (1) the triage acuity scale, (2) type of pathology (medical, surgical-traumatological, psychiatric), (3) experience of the caregiver expressed in years since certification, (4) patient age, (5) patient sex, (6) workload represented by the number of patients present in the emergency room, (7) time of day or night, (8) day of the week, and (9) month of the year (seasonal variability). To account for the possible effect of exogenous factors that would impose an asymmetry in the data (skewness on the right) by extending the awareness of laboratory results, we will identify these factors as the study progresses prospectively and take them into account in the final analysis. The same analyses will be performed for the nurses. We will carefully monitor and evaluate through descriptive analyses any differences between nurses’ and physicians’ frequency access to laboratory results. If the target sample size cannot be reached, we will first extend the prospective data collection period by 3 months (deemed ethically acceptable as not impacting patients) or present only the results of qualitative user experience interviews.

For the technology acceptance self-administered survey questionnaire, scores on the 8 technology acceptance constructs will be described using descriptive statistics. Items on the SUS questionnaire will be described using frequencies. Analyses will be carried out using R software (R Core Team) [27]. All statistical tests will be 2-sided, with an α risk of .05.

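### Four of the nine covariates in the adjusted model are patient-level variables that the protocol says it will not collect

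*Protocol article*

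**What the plan says.** Data Collection describes an extract from the institutional data lake: the time stamp at which a laboratory result is issued, and the time stamps at which caregivers open it in the electronic record or the app. It closes the list with "No other patient-level data such as identifiers or clinical characteristics will be collected".

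Statistical Analysis gives case-mix and physician differences as the reason for a multivariable GEE and lists nine covariates. The first two are "1) the triage acuity scale, (2) type of pathology (medical, surgical-traumatological, psychiatric", the third is "3) experience of the caregiver expressed in years since certification", and the fourth and fifth are "4) patient age, (5) patient sex". The sixth is "6) workload represented by the number of patients present in the emergency room". The last three are time of day, day of the week and month.

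Two other places bear on the point. The secondary outcomes under Outcomes and Measures include mean ED length of stay per patient, from triage to departure, taken from the hospital's administrative database. For caregivers, Table 2 lists "Case report form (demographics", ticked only at enrolment, and the Participants section says "Written informed consent will be obtained from each participant in the experimental group".

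**The concern.** The two periods are not randomised and not concurrent. Twelve months before the app are compared with the six months from November 2022 to April 2023, and the protocol itself calls the groups nonequivalent. Covariate adjustment is the means it names for dealing with case-mix and staff differences between them.

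If the extract follows Data Collection to the letter, the variables that describe the patient never reach the analysis file. The listed model cannot then be fitted, and any difference between the periods in acuity, type of problem, age or sex stays in the estimated app effect on the primary outcome. If the extract instead follows Statistical Analysis, the article misdescribes which patient data the study takes. Either way, one section is wrong as it stands. This is a conflict between two explicit statements, so it is not a detail that a fuller document could simply supply.

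**Working it through.** **The plan's own figure.** The only calculated figure is the sample size, and it is sound on its own terms. Inputs from Sample Size and Statistical Analysis: difference 0.5 SD, two-sided 5%, power 90%, intraclass correlation 0.1, and 100 patients a month for 3 months, so 300 per physician.

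- Per period: 2 × (1.960 + 1.282)² / 0.5² = 84.06, rounded up to 85; both periods, 170.
- Design effect: 1 + (300 − 1) × 0.1 = 30.9.
- Total: 170 × 30.9 = 5253, as stated; 5253 / 300 = 17.5, so 18 physicians.

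No covariate enters this calculation, so the sample size is unaffected by what follows.

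**Each covariate against its stated source.**

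| No. | Covariate | Level | Position under Data Collection as written |
|---|---|---|---|
| 1 | Triage acuity | Patient, clinical | Excluded |
| 2 | Type of pathology | Patient, clinical | Excluded |
| 3 | Caregiver experience | Caregiver | Not touched by the sentence; no pre-period source stated |
| 4 | Patient age | Patient | Excluded |
| 5 | Patient sex | Patient | Excluded |
| 6 | Number of patients present | Department count | Not clearly excluded; source not stated |
| 7 to 9 | Time of day, weekday, month | Time stamp | Available, assuming the date is kept with the clock time |

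Count: 4 of 9 directly contradicted (1, 2, 4, 5); 1 of 9 with no stated pre-period source (3); 4 of 9 not contradicted (6 to 9).

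**What is left.** With the four removed, the remaining terms describe the department, the calendar and, if obtained, the caregiver. None describes the patient.

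**Length of stay.** Triage and departure times for each patient are patient-level data beyond the laboratory time stamps. Read literally, the Data Collection sentence rules them out. Outcomes and Measures says they will be extracted, although from a different database.

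**Caregiver experience.** The one form named for demographics is scheduled at enrolment, and consent is described for the experimental group only. The protocol therefore states no source for caregivers who worked only in the pre-period. It does not say that such data will not be obtained.

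**The case against.** The strongest reply is that the restrictive sentence was never meant to cover the whole study. It sits in a paragraph about the data-lake query. Length of stay is given its own source elsewhere, and Ethics Approval says that the team will work with coded, de-identified data. On that reading the sentence is loose wording and the covariates will be extracted. This is plausible, but the sentence is unqualified and names clinical characteristics expressly. The document does not show which section holds the error. It could equally be a deliberate limit, since the no-objection declaration rests on the study examining effects on health care providers.

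A second reply is that the month term picks up part of the case-mix. It can absorb a seasonal pattern that is common to both periods. It cannot absorb a change in patient mix from one year to the next.

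The objection does hold against several stronger readings that a reader might infer:

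- That the four variables will not exist. Data Collection says the data lake holds all data and events of the electronic record system, so they should be available at source. The conflict is over whether they will be extracted.
- That five covariates are lost. Experience is a caregiver variable, which the sentence does not address.
- That experience is missing for the entire pre-period, so that a complete-case fit would drop every control record. This would follow only if no other source were used and no caregiver worked in both periods. The Setting section gives a four-month period for residents only; fellows and nurses may well span both periods, and the overlap is not stated.
- That no adjusted model can be fitted. A GEE with the remaining covariates can be, and the first GEE described needs none.
- That the question about in-app alerts is blocked. An abnormal flag belongs to the laboratory result, and a coded visit key is not clearly an excluded identifier.

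**Conclusion.** The contradiction stands and should be resolved before the data are extracted. Four of the nine listed covariates are patient-level variables that Data Collection says will not be collected, and they are the whole of the patient case-mix adjustment. If that section is followed, the nine-covariate model cannot be fitted as listed. A reduced model can be, but it does not meet the stated purpose of adjusting for case-mix. The wording also conflicts with the length-of-stay outcome.

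The absence of a stated pre-period source for caregiver experience is a lesser point, inferred from Table 2 and the consent wording.

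The size of any resulting bias cannot be computed, because the protocol gives no case-mix figures for either period. The conclusion rests on reading the Data Collection sentence literally and assumes nothing about which section was intended.

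**What to change.** Reconcile Data Collection, Outcomes and Measures, and Statistical Analysis. Replace the restrictive sentence with a fixed, coded, de-identified list of fields, identical for both periods, that adds triage level, type of pathology, age and sex to the laboratory time stamps, with triage and departure times for length of stay. State the source of each covariate. For pre-period caregivers, take years since certification from coded staff records. Professional grade would not be an adequate substitute: the analysis is repeated for nurses alone, among whom it is constant.

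The cost is a few more query fields and a check that the extract agrees with the basis of the no-objection declaration under Ethics Approval, possibly with a notification. No new patients or procedures are needed.

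If the restriction is intended, delete the four covariates from Statistical Analysis, state there and under Limitations that patient case-mix is not adjusted for, and reword Data Collection so that it allows the length-of-stay times.

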### Blinding

Although neither the participants nor the study investigators can be blinded to the intervention, both will be blinded to the results of the study until their final analysis by the statistician. Participants will be informed only of the overall purpose of the study, which is to evaluate the effects of the app on quality of care, but not about the aim of reducing the time to access laboratory results in order to minimize bias. The statistician will remain blinded to allocation until the final analysis.

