## Methods

### Study Design

We will conduct an 18-month, single-center, nonequivalent comparison group, pre-post study. We will compare the control and experimental groups on outcome measures before (12-month period) and after (6-month period) the implementation and use of the app. This study protocol adheres to the Standard Protocol Items: Recommendations for Interventional Trials 2013 Checklist [18]. All data will be deidentified. The study will be conducted according to the principles of the Declaration of Helsinki [19] and Good Clinical Practice guidelines [20]. It is our intention to present these at scientific congresses and to publish the results in an international peer-reviewed journal, irrespective of the magnitude or direction of effect. Only deidentified data will be available to researchers for analysis. The study is registered at ClinicalTrials.gov on September 28, 2022 (NCT05557331).

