## Results

Retrospective laboratory data will be arbitrarily collected from October 31, 2021, to October 31, 2022. Prospective data will be collected from the start of enrollment on November 1, 2022, through April 30, 2023. We anticipate an analysis of the results by mid-2023 and expect the results to be published in late 2023.

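### The statistician cannot be blinded to a group defined by calendar period, and the stated blindness to results is not reconciled with the plan to find outcome-related factors while the app period runs

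*Protocol article*

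**What the plan says.** The Blinding section of the protocol article concedes that participants and investigators will know about the intervention. It then makes two claims. For participants and investigators, "both will be blinded to the results of the study until their final analysis by the statistician". For the analyst, "The statistician will remain blinded to allocation until the final analysis".

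The design is given under Study Design: "We will conduct an 18-month, single-center, nonequivalent comparison group, pre-post study", comparing outcomes "before (12-month period) and after (6-month period) the implementation and use of the app". The Results section supplies the dates: "Retrospective laboratory data will be arbitrarily collected from October 31, 2021, to October 31, 2022" and "Prospective data will be collected from the start of enrollment on November 1, 2022, through April 30, 2023".

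Access is logged differently in the two periods. Before implementation it is the first opening of the laboratory viewer in the medical record. Afterwards, under Data Collection, it is the opening of a push notification or of the app's own results page, and Procedure and Intervention adds any workstation access that occurs alongside or instead.

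Statistical Analysis lists month of the year, day of the week and time of day among the covariates. It also says that outside factors which delay awareness of results, and so skew the times to the right, will be identified during prospective collection and taken into account at the final analysis. Separately it says: "We will carefully monitor and evaluate through descriptive analyses any differences between nurses’ and physicians’ frequency access to laboratory results".

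**The concern.** Blinding a statistician to allocation means something when a concealed assignment can be kept out of the analyst's view. Here the only thing that separates control from app records is the date on which they arose. If the data reveal the period, the sentence describes a protection that the study does not have, and readers will credit it.

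This matters because the study is open and nonrandomised, and it measures access by different routes before and after. Decisions on which time stamp counts, which records are dropped and which late-found factors enter the model can move the primary comparison. The factor search is the sharpest case. The factors are defined by their effect on the primary outcome, and they are looked for in the prospective period, whereas the control year is retrospective. If long delays were explained or adjusted away in the app period only, the comparison would tilt towards the app.

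**Working it through.** The plan states no figure for masking. The check is whether a neutrally coded period label (A or B) could stay hidden in the data described.

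**Inputs.** Control 31 October 2021 to 31 October 2022, app 1 November 2022 to 30 April 2023 (Results). Periods of 12 and 6 months (Study Design). Month as covariate (Statistical Analysis). App time stamps (Data Collection; Procedure and Intervention). 35,000 visits a year and about 16,600 in the intervention period (Setting).

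**Period length.** The stated lengths give 12 / 6 = 2. Counting both end dates, control has 366 days and app has 181, and 366 / 181 = 2.02. If records accrue roughly in proportion to days, the larger coded group is control. The visit figures point the same way: 35,000 / 16,600 = 2.11, if the annual volume applies to the control year.

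**Month coverage.** The app period contains only November to April. May to October 2022 has 31 + 30 + 31 + 31 + 30 + 31 = 184 days, and 31 October 2021 adds one, giving 185 days found only in control.
- Share of control days: 185 / 366 = 51%.
- Share of all study days: 185 / (366 + 181) = 185 / 547 = 34%.

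A cross-table of coded group by month would have six empty cells in one group. The month covariate therefore reveals the code as soon as it is tabulated.

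**Access route.** Notification and app-page time stamps can arise only after implementation. Any group containing them is the app group.

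**Row level.** Control has 366 - 185 = 181 days in November to April, the same number as the app period. With the year removed, a record from those months opened at a workstation need not reveal its period. The dataset is unmasked; each row is not necessarily so.

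**Blindness to results, set against Statistical Analysis.**

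| Text in Statistical Analysis | Timing | Quantity | Conflict with blindness to results? |
|---|---|---|---|
| Search for factors that lengthen awareness | During prospective collection | Tied to time to access, the primary outcome | Unresolved: who looks, and at what data, is not said |
| Nurse and physician access frequency | None given | Frequency by profession | Not shown: it is not elapsed time by period |
| Extension by 3 months | If the target number is not reached | A count | No |

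**The case against.** The strongest defence is that the article nowhere puts a full calendar date in the analysis file. The covariates are month, weekday and time of day, and the times are specified as clock times. Who runs the extraction is not stated, so the statistician might receive only derived elapsed times. This stands against the stronger reading that every record discloses its group. It does not rescue the sentence, because month coverage, group size and the presence of app time stamps unmask the file in aggregate.

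A second defence leans on the words about the final analysis: the statistician may simply not look until then. On that reading the statistician is waiting, and the analysis itself is not masked.

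A reader might also infer that investigators see results while the study runs. The document does not support that. The frequency monitoring carries no timing, concerns profession rather than elapsed time before and after, and does not separate the statistician from the rest of the team. The extension rule turns on a sample count. That control data already sit in the hospital's data store does not show that anyone has analysed them, and on their own they contain no comparison. Some delaying factors could also be logged without seeing access times.

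Finally, the outcome is system-logged, the access stamps are defined, and the model and nine covariates are named. Locked queries and exclusion rules are commonly left to an analysis plan, which is not shown. Their absence from the article is therefore not the point here; the point is a stated safeguard that the design cannot provide.

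**Conclusion.** The claim that the statistician is blinded to allocation does not hold for this design. Group equals calendar period, and three features of the planned data each identify it at dataset level: six months of the year that occur only in control (51% of control days), a size ratio of about 2 to 1, and time stamps that exist only with the app. The size argument assumes records accrue roughly in proportion to days; the other two do not need that.

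The claim that investigators and participants are blind to results is different. Withholding the pre-post comparison from them is achievable, so it need not be deleted. It is, however, in unresolved tension with the identification of delay-causing factors during the app period for use in the final analysis. This is an inconsistency to settle, not proof that anyone sees results.

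No shift in the estimated effect can be calculated from the document. What is at issue is exposure to data-driven choices and a description that overstates protection. It should be corrected.

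**What to change.** 1. In Blinding, delete the statement that the statistician is blinded to allocation, and say that the analysis is not masked to period.
2. Keep the commitment that the pre-post comparison of access times is withheld from investigators and participants until the final analysis. In Statistical Analysis, say who sees which access data before then.
3. Fix and date the extraction query, the definition of access, the exclusions and the model before any post-period access time is extracted. If the analysis plan already does this, cite it.
4. Require the outside factors to be chosen without sight of access times by period, and applied in the same way to both periods.
5. Limit any monitoring before that lock to counts, such as enrolled caregivers and eligible results. Place the nurse and physician frequency comparison after it.

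The cost is protocol wording and a dated lock. The downsides are a less favourable description of blinding and no early look at access behaviour. A factor that cannot be recorded for the retrospective year could not be used as an adjustment.
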